#### Secondary Outcomes

Post discharge falls data from participants recruited at the SDH site will be analysed using the same approach as falls data collected while participants are in hospital.

Length of stay in hospital will be compared between groups using Cox semi-parametric regression analysis (single event) which permits adjustment for covariates as required. Health-related quality-of-life assessments undertaken using the EQ-5D will be converted into summative "utility" scores using the Dolan formula.[45] Change in health-related quality-of-life during hospitalisation will be compared between groups using linear regression where the discharge measure is the dependent variable and adjustment is made for both admission assessment and length of time between assessments.

Data Management and Analysis will be completed using Stata version 10.0 software (Stata Corp, Texas).

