**Methods and design:**

A prospective randomised controlled trial (n = 1206) is being conducted at two hospitals in Australia. Patients are eligible to be included in the trial if they are over 60 years of age and they, or their family or guardian, give written consent. Participants are randomised into three groups. The control group continues to receive usual care. Both intervention groups receive a specifically designed patient education intervention on minimising falls in addition to usual care. The education is delivered by Digital Video Disc (DVD) and written workbook and aims to promote falls prevention activities by participants. One of the intervention groups also receives follow up education training visits by a health professional. Blinded assessors conduct baseline and discharge assessments and follow up participants for 6 months after discharge. The primary outcome measure is falls by participants in hospital. Secondary outcome measures include falls at home after discharge, knowledge of falls prevention strategies and motivation to engage in falls prevention activities after discharge. All analyses will be based on intention to treat principle.

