#### Secondary research questions

2. Does providing individual patient education for older patients in addition to usual care affect the rate of falls after discharge compared to providing usual care alone?

3. Does providing individual patient education in addition to usual care affect patient length of stay in hospital or change in health related quality of life during admission?

4. Does providing individual patient education for older patients in addition to usual care influence patients' pre – discharge self – perceived risk of falls, knowledge about falls and falls prevention, motivation to engage in self protective strategies in the first six months after discharge, or their levels of participation in falls prevention activities after discharge?

5. Does providing face-to-face health professional follow up in addition to multimedia patient education and usual care reduce falls compared to providing multimedia patient education and usual care?

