### Outcome measures

The primary outcome measure is participant falls during both hospitalisation and the 6 month post discharge period. The definition of a fall used in this study is the World Health Organisation definition namely: "any event when the participant unexpectedly comes to rest on the ground, floor or another lower level."[37]

Secondary outcome measures being collected include length of stay in hospital, and change in health-related quality of life during hospitalisation, quantified using the EQ-5D instrument.[38] The EQ-5D is administered by face-to-face interview, with the question set presented to the participant in hard copy and read out by a research assistant.

Secondary outcome measures for participants in the home follow up sub-trial at the SDH site include a pre-discharge assessment using a survey (see additional file 1) of their self perceived risk of falls and falls injuries, knowledge about falls mechanisms, awareness of strategies to prevent falls at home and confidence and motivation to prevent falls at home after discharge. The survey items were developed by the investigative team during a previous randomised trial of the education materials.[28]

The final outcome survey (see additional file 2) administered to participants in the home follow up trial measures participants' engagement in falls prevention activities. The activities specified in the survey items were selected on the basis of current evidence for falls risk reduction when implemented amongst older community dwelling people.[39,40]

Demographic data being collected includes age, gender, falls in the 6 months prior to hospitalisation, admission and discharge residential living status, cognitive status using the Short Portable Mental Status Questionnaire,[41] mood using the Geriatric Depression Scale,[42] and medical diagnosis on admission.

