### Procedure

Prior to commencement of recruitment, hospital staff working in participating wards were trained to apply the WHO definition of a fall, using 14 video-scenarios. This training was necessary as previous research indicates that absence of a definition is a barrier to documenting falls and that providing a written definition of a fall in itself does not considerably improve agreement between hospital staff as to what constitutes a fall.[43,44]

Baseline measurements are collected from participants after written consent has been obtained (or in the case of patients with cognitive impairment, where their carer or family has provided written consent). Participants are then randomised into one of the 3 groups. Participants in group 1 then continue to receive 'usual care'. Participants in group 2 receive the patient education via DVD and written workbook in addition to usual care. These participants have an opportunity to view the DVD within 24 hours of being allocated to this intervention. If the participant is too unwell to view the DVD immediately, they are provided with an opportunity to view the DVD as soon as practical after their health condition stabilizes. Participant family members, care-givers, or guardians are also invited to view the DVD and the workbook on regular workdays. Participants are asked if they wish to view the DVD again on a weekly basis until discharge and are encouraged to review their goals via interactive use of their workbook. The intervention is identical to that provided for participants in group 3 with the exception that there is no health professional follow-up visit. Participants in group 3 receive the patient education intervention described in group 2 and also receive the individual health professional follow-up visits. The health professional monitors these visits for time, content and participants' knowledge and achievement of their planned strategies.

This is a pragmatic trial and the interventions are provided in the usual hospital environment, most often at the bedside. Participants receive the intervention at a convenient time for optimal engagement. For example, if a participant becomes acutely unwell the investigator returns to complete the intervention when the participant is medically stable.

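### The quality-of-life regression adjusts for time from baseline to discharge, in effect a length of stay that the trial also tests as an outcome, so its group coefficient need not be the total effect of allocation

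*Protocol article*

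**What the plan says.** Under Data Analysis, Secondary Outcomes, change in utility during hospitalisation is compared by "linear regression where the discharge measure is the dependent variable", and "adjustment is made for both admission assessment and length of time between assessments".

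The timing of the two assessments is fixed elsewhere in the article. Under Procedure, "Baseline measurements are collected from participants after written consent has been obtained" and "Participants are then randomised into one of the 3 groups". The Abstract (Methods and design) says "Blinded assessors conduct baseline and discharge assessments".

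Length of stay is itself an outcome. The third research question asks whether education would "affect patient length of stay in hospital or change in health related quality of life during admission". Outcome measures states: "Secondary outcome measures being collected include length of stay in hospital, and change in health-related quality of life during hospitalisation". The Secondary Outcomes section then compares stay between groups by single-event Cox regression.

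The article describes no quality-of-life model without the time term and gives no reason for including it.

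**The concern.** The first assessment precedes allocation and the second is fixed by the discharge date. The interval is therefore the stay from enrolment onwards, which is the part of the stay that education could alter. The plan tests that quantity as a possible effect of education and then holds it constant when it tests quality of life.

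This can distort the comparison in two ways. Any effect on utility that runs through duration of stay is taken out of the group coefficient. And if an unmeasured factor such as frailty drives both stay and discharge health, comparing patients at equal stay compares groups that randomisation no longer balances.

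An effect on stay cannot be assumed away. The Background links falls to longer stay, and the Sample size section anticipates a 30% lower fall rate. At stake is whether the quality-of-life half of the third research question gets the answer it asks for.

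**Working it through.** The article gives no figure for this analysis, so there is none to reproduce. From the plan I use 402 patients per group and 24% fallers in the control group, reduced by one third to 16%. All other inputs below are assumptions.

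**1. Identity.** For least squares, with everything conditional on admission utility:

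adjusted group effect = total group effect - λ × δ

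δ is the group difference in stay and λ is the within-group slope of discharge utility on stay. The two effects agree if δ = 0 or λ = 0. Otherwise the sign of the gap depends on the signs of both.

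**2. Frailty as a shared cause, no true effect on utility.** Assume that one SD of frailty adds 8 days to stay (residual SD 14 days) and lowers discharge utility by b = 0.06 to 0.12. Leaving admission utility aside for the hand calculation:

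- λ = -b × 8 / (8² + 14²) = -b × 8/260
- b = 0.06, stay 2 days shorter: 0 - (0.06 × 8/260) × 2 = -0.0037
- b = 0.12, stay 4 days shorter: 0 - (0.12 × 8/260) × 4 = -0.0148

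Admission utility absorbs part of frailty. A large linear simulation gave -0.0026 and -0.0058 for 2 days, and -0.0059 and -0.0118 for 4 days. Without the time term the effect was within 0.0004 of zero.

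**3. Trial-sized simulation.** 402 per arm, 1,500 runs, two-sided 5% test. Stay is log-normal with log-mean 2.7. Where frailty is present, it shifts log stay by 0.5 and utility by -0.1 per SD. The residual SD is 0.5 for log stay and 0.2 for utility. With frailty, mean control stay is exp(2.7 + 0.25) = 19.1 days, so 10% and 20% shorter means about 1.9 and 3.8 days.

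| Scenario | Effect without / with time term | Rejection rate without / with |
|---|---|---|
| Stay unchanged, no utility effect, frailty | 0.000 / 0.000 | 4.4% / 4.9% |
| Stay 10% shorter, no utility effect, frailty | 0.000 / -0.008 | 5.1% / 8.6% |
| Stay 20% shorter, no utility effect, frailty | 0.000 / -0.017 | 4.7% / 19.4% |
| Stay 20% shorter, no utility effect, no frailty | 0.000 / 0.000 | 5.3% / 5.5% |
| Stay 20% shorter, true effect 0.05, frailty | 0.050 / 0.033 | 89% / 59% |
| Stay 20% shorter, benefit only through stay, no frailty | 0.013 / 0.000 | 16% / 4% |
| Stay unchanged, true effect 0.05, frailty | 0.050 / 0.050 | 89% / 91% |

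**4. Direction.** Keep step 2 and let each day in hospital add 0.004 utility, as recovery in rehabilitation might. With stay 4 days shorter, the total effect is -4 × 0.004 = -0.016.

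- b = 0.06: λ = 0.004 - 0.00185 = 0.00215, adjusted effect = -0.016 + 4 × 0.00215 = -0.007
- b = 0.12: λ = 0.004 - 0.00369 = 0.00031, adjusted effect = -0.016 + 4 × 0.00031 = -0.015

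Here the time term makes education look better than its total effect. At 0.002 per day, λ is 0.00015 or -0.00169, so the direction turns on the strength of frailty.

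**5. Falls.** Assume a loss of 0.15 utility per faller. The total effect is 0.08 × 0.15 = 0.012. Let a faller stay k extra days and take b = 0.06. The mean within-group variance of the faller indicator is (0.24 × 0.76 + 0.16 × 0.84)/2 = 0.1584.

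- k = 5: λ = -(0.15 × 5 × 0.1584 + 0.48)/(260 + 3.96) = -0.00227, δ = -0.4, adjusted effect = 0.011
- k = 10: λ = -(0.15 × 10 × 0.1584 + 0.48)/(260 + 15.84) = -0.00260, δ = -0.8, adjusted effect = 0.010

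Most of the fall-related benefit remains after adjustment.

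**The case against.** The strongest defence is that patients are reassessed after different intervals, so a comparison at equal elapsed time is reasonable. That would serve if timing were a scheduling nuisance. Here timing is set by discharge, which education may change, and the article states no such rationale. The time-adjusted model answers a different question from the effect of providing education.

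Other points limit the concern, and they stand:

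- A reader might infer that the group effect is biased outright. It is not, unless education changes stay and stay is related to discharge utility (steps 1 and 3).
- A reader might infer that adjustment must make education look worse. Location and Setting includes wards for longer rehabilitation, where more days may mean more recovery, and step 4 shows the reverse.
- A reader might infer that all benefit of avoiding falls is removed. Only the part running through duration is (step 5).
- A reader might see a breach of intention to treat. A covariate changes neither who is analysed nor in which group; the issue is which effect is estimated.
- A shift of 2 to 4 days may be generous. If stay changes only through 8 percentage points fewer fallers, it needs 2/0.08 = 25 to 4/0.08 = 50 extra days per faller. At an assumed 10 days the shift is 0.8 days, and scaling step 2 gives about -0.001 to -0.002. Even -0.012 is below one standard error: √(2/402) × 0.20 to 0.25 = 0.014 to 0.018, with the SD assumed.

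**Conclusion.** The concern holds as a conditional, structural point. The plan fixes a covariate that is essentially post-randomisation length of stay, which it also tests as an outcome, and nothing else in the article corrects this. That the interval starts at enrolment rather than admission does not weaken the point, because it keeps the part of the stay that follows allocation.

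If education alters stay and stay is related to discharge utility, the adjusted coefficient is not the total effect of allocation, and it can err in either direction. If education leaves stay unchanged, there is no bias. The third research question leaves that open, so the model should not depend on it.

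The size is unknown. Under the assumed frailty values and a stay 2 to 4 days shorter, the spurious difference is about -0.003 to -0.012 utility; smaller shifts give less, and the second set of assumptions (step 3) reaches -0.017. The primary falls analysis and the sample size are untouched.

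**What to change.** Make the main quality-of-life model a regression of discharge utility on group and admission utility, with further covariates only if measured before randomisation. Report the model with time between assessments as a labelled secondary analysis, and say that it compares groups at equal elapsed time and does not estimate the total effect of allocation.

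This takes one term out of the main model and needs no new data. The cost is at most a small change in precision: in the simulated case where stay is unchanged and the true effect is 0.05, power is 89% without the term and 91% with it.

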#### Sample size

Recent economic modelling of patient education for prevention of falls indicates this intervention may be a cost-effective approach for the prevention of falls with reductions in the proportion of people who fall in the order of 20% and possibly as low as 10%[12]. Previous in-hospital investigations have demonstrated reductions in falls per 1000 patient days in the order of 30% using targeted, multifactorial interventions, [17] and amongst specific patient subgroups as high as 49% using patient education alone[27]. Given this background context, and that the education is being provided to a reasonably unselected patient cohort, we anticipated that this intervention could reduce the rate of falls per 1000 patient days by 30%.

We conducted 1000 bootstrap simulations of data previously published from this setting [17] and determined that our experiment would have 80% power to detect a reduction in the rate of falls of 30% in one of the intervention groups relative to the control group during the inpatient period. This assumes a sample size of n = 390 per group, that the control group has a rate of falls of 15.7 per 1000 patient days, use of a Cox semi-parametric proportional hazards regression (Anderson-Gill extension for recurrent events) analysis approach and a two-tailed alpha of 0.05. Given that previous research in this setting similar to the present trial has been completed with no drop-outs, [17] we will recruit only an additional 3% of patients per group culminating in a sample size of n = 402 per group (n = 1206 in total). This sample size will also have 80% power to detect a one-third reduction in the proportion of patients who are fallers assuming that 24% of those in the control group will become fallers during their hospitalisation. The follow-up cohort of n = 117 per group will have 80% power to detect a 33% reduction in the proportion who are fallers assuming that 58% of the control group become fallers during the 6 month follow-up [46].

#### Ethics Approval

Ethics approval was obtained from the Medical Research Ethics Committee at The University of Queensland (project number2007000148). The trial is registered with the Australian Clinical Trials registry: ACTRN12608000015347.

## Results

It is estimated that recruitment for the trial will be completed in April 2009. Data collection for the post discharge follow up cohort of 350 participants from SDH is anticipated to be completed by October 2009.

## Discussion

Patient behaviour is an integral contributing factor in many in-hospital falls.[7,24,25] In wards where patients are encouraged to regain their mobility and independence, a balance exists between encouraging patient activity and restricting activities to only those that a patient can perform safely. Staff commonly direct patients as to how much assistance they require, [17] however intrinsic patient factors such as cognitive impairment, inability to follow directions, confusion, and poor judgment may impede patient compliance with hospital staff recommendations. These factors have consistently been identified as significant risk factors for in-hospital fall s[47].

Falls risk reduction strategies such as alerting staff prior to mobilising and using equipment safely rely on patient adherence. Our education is based on a preventative health model of education [29] which proposes that patient adherence can be enhanced if patients have an awareness of the risks they face and furthermore have the knowledge and skills to perform strategies that could reduce their risk of falls. We argue that participants will be more likely to engage in safer behaviours when firstly they believe that the behaviour is likely to result in a beneficial outcome and secondly when they have sufficient self efficacy (confidence) to perform their strategies. Behaviour initiation may also be mediated by individual beliefs and approval of family and staff when participants undertake falls prevention strategies, thereby enhancing the desired behaviours. Finally our education aims to address barriers and misconceptions in a manner that enhances participants' comprehension and belief in the beneficial effect and achievability of falls prevention behaviours.

Previous studies have identified a consistent decline in functional status in older people post discharge [46,48] and a substantial increase in rates of falls in the first month after discharge.[11] Older patients may find it difficult to accurately assess their early mobility post injury or illness, when their functional status has not returned to pre-admission levels. Exploration of the link between participants' self-perceived risk of falls, knowledge of falls epidemiology, falls prevention strategies and motivation to undertake falls prevention strategies on discharge and participants' rates of falls and engagement in falls prevention activities after discharge will clarify the possible role of in-patient education in preventing falls in this population.

The strengths of this study include its size (n = 1206, the previous largest in this field with randomization of individual patients is n = 626), use of a randomised controlled trial approach, the use of multiple avenues for collating data on falls in hospitals, preparatory training of hospital staff to identify falls and use of assessors blinded to participant group allocation in the collation of outcome measures. The study has wide inclusion criteria for a hospital population of older people across two disparate geographical sites indicating that the findings of this research will be broadly applicable. The intervention employs a previously validated, empirically tested health education model as a framework for its development [29] This model for conceptualising health behaviours has previously been successfully used in a wide range of health areas, but to the researchers' knowledge this is the first time the HBM has been used in the area of falls prevention in hospital.

The study is not powered to show the effect of falls prevention education on falls injuries in hospital and after discharge. It has not been possible to blind ward staff to the intervention and it is possible that ward staff, after exposure to the intervention, have adapted their behaviour to study participants or to falls reporting. It is also possible that some participants discuss their strategies or treatment with participants allocated to the control group resulting in a dilution effect. Participants are drawn from a high risk population and continued participation may be affected by acute illness such that a participant becomes too medically unwell to receive the full intervention or is transferred to another hospital for urgent medical care and cannot continue to be monitored or receive the intervention.

## Conclusion

Uncertainty about the most effective interventions to reduce the high individual and societal cost of falls provides a compelling rationale for further large, well designed randomised trials to determine the most effective clinical interventions to reduce falls and falls injuries in older people, both in hospital and after discharge.[49] This is the first randomised controlled trial to examine the effect of patient education alone as an intervention to prevent falls in hospital and falls at home after discharge compared to providing usual care. The results of this study will provide robust recommendations for clinicians and researchers about the role of patient education in this population. This intervention is easily translated from the research to the clinical setting and could be duplicated across a very broad range of hospital environments.
